### Sample Size

#### RCT1: High-Dosage Intervention (2-Week Home vs On-Site Camp)

Sample size calculation was performed using PASS (version 14.0.15; NCSS) for a one-sided noninferiority *t* test comparing 2 independent means. The analysis was based on the mean improvement in GMFM-66 observed in the study of Bleyenheuft et al [7]. We hypothesized that there would be a true difference of Gross Motor Function Measure (GMFM) units between groups, with an α of .05 and a 1-*β* of 0.9. We estimate that the noninferiority margin (NIM) could reach a maximum of 2 GMFM units since this value is the minimal clinically important difference (MCID) of the GMFM-66. The data are drawn from populations with SDs of 1.9 GMFM units. Consequently, 17 participants are needed per group (N=34). Considering 25% potential dropouts per group, 44 participants will be included.

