#### RCT1: High-Dosage Intervention (2-Week Home vs On-Site Camp)

Changes within each intervention group between baseline and post intervention (T1-T0) will first be assessed. Paired-sample *t* tests will be used when data are normally distributed, while the nonparametric Wilcoxon signed-rank test will be applied in the case of nonnormal distributions.

Noninferiority analyses will be performed by comparing changes obtained between groups (mean change in the HABIT-ILE@home group minus the HABIT-ILE on-site group). The mean obtained difference and its 95% CI will be compared to the prespecified NIM. The NIM has been set for each outcome measure based on the MCID.

For normally distributed data, the between-group difference and its CI will be estimated using an independent samples *t* test (or Welch *t*-test when variances are unequal). When the assumption of normality is not verified, Mann-Whitney *U* tests will be applied.

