#### RCT2: Low- to Moderate-Dosage Home Follow-Up Interventions (9-Weeks HABIT-ILE@home Follow-Up vs Nonspecific Home Follow-Up)

Changes within each group during follow-up (T2-T1) will be assessed using paired-sample *t* tests when data are normally distributed, or Wilcoxon signed-rank tests in the case of nonnormal distributions.

The superiority analysis will be based on between-group comparisons using an analysis of covariance (ANCOVA) model. For each outcome, the model will be specified as outcome at T2 ~ outcome at T1 + RCT1_group × RCT2_group. This model will include the baseline value at T1 as a covariate and will test the main effects of the initial intervention (HABIT-ILE@home vs on-site), the follow-up intervention (HABIT-ILE@home follow-up vs nonspecific home follow-up), and their interaction. This approach will allow the effect of the second randomization (RCT2) to be evaluated while accounting for the initial allocation in RCT1.

The inference for superiority will be based on the main effect of RCT2_group (HABIT-ILE@home follow-up vs nonspecific home follow-up), adjusted for T1 values and RCT1_group. The interaction term (RCT1_group × RCT2_group) will be examined to explore whether the effect of the follow-up intervention differs depending on the initial intervention.

For normally distributed outcomes, model assumptions will be checked and standard ANCOVA estimates will be used. If normality is not verified, a nonparametric alternative based on rank-transformed ANCOVA will be applied.

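### In RCT1, the Mann-Whitney fallback for non-normal data gives, as written, no estimate or confidence interval to compare with the 2-unit noninferiority margin

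*Protocol article*

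**What the plan says.** The RCT1 part of Statistical Analysis defines the contrast as mean change in the home group minus mean change in the on-site group, and gives one decision rule: "The mean obtained difference and its 95% CI will be compared to the prespecified NIM". The next paragraph says where the interval comes from. For normally distributed data it is an independent-samples t test, or Welch's version if variances differ. For other data: "When the assumption of normality is not verified, Mann-Whitney" U tests are used. That branch names no effect estimate, no interval, no shift by the margin and no decision rule.

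The RCT1 part of Sample Size plans "for a one-sided noninferiority" t test "with an α of .05". It says the margin "could reach a maximum of 2 GMFM units since this value is the minimal clinically important difference (MCID) of the GMFM-66", and it states: "The data are drawn from populations with SDs of 1.9 GMFM units". The RCT1 primary outcome is the change in GMFM-66 from T0 to T1, so this rule and its fallback govern the main conclusion.

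For RCT2 the corresponding sentence is: "If normality is not verified, a nonparametric alternative based on rank-transformed ANCOVA will be applied".

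**The concern.** A noninferiority conclusion needs a statement about a specific deficit, here 2 GMFM-66 units. The ordinary Mann-Whitney test asks whether one group tends to have larger values than the other. Its null is no difference, and the margin never enters. If the normality check fails, the analyst holds a p-value for the wrong hypothesis and has no interval to compare with -2.

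Two outcomes are then possible. Either the primary question has no planned answer, or someone improvises one after seeing the data. The obvious improvisation is to treat p>.05 as noninferior, which is unsound with about 20 children per arm.

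**Working it through.** **1. What the trial was sized for.** Inputs from Sample Size, RCT1: margin 2, SD 1.9, one-sided alpha .05, power 0.90. The number for the true difference does not appear in the text, so 0 is assumed.

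- Normal approximation: n = 2 × SD² × (z₀.₉₅ + z₀.₉₀)² / margin² = 2 × 3.61 × (1.645 + 1.282)² / 4 ≈ 15.5, so 16 per group.
- Exact noncentral t with n = 17: noncentrality = 2 / (1.9 × √(2/17)) ≈ 3.07 on 32 df, power 0.913. Seventeen is the smallest n that reaches 0.90.

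The stated 17 per group is reproduced. The trial is sized on a mean difference tested against the margin.

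**2. What the fallback tests.** With home changes xᵢ and on-site changes yⱼ, U counts the pairs with xᵢ > yⱼ and is compared with its distribution under no difference. The value 2 appears nowhere. To test the margin one would count pairs with xᵢ + 2 > yⱼ, or invert that test to get a Hodges-Lehmann shift with its CI. The plan states neither.

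**3. What happens if p>.05 were taken as noninferior.** This reading is an assumption, not the plan's. Simulation: location shift, SD 1.9 in both arms, 20,000 trials per setting, two-sided Mann-Whitney at .05, true home deficit exactly 2. The test is applied to every simulated trial, not only to those that fail a normality check.

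| Shape of change score | 17 per arm | 22 per arm |
|---|---|---|
| Gamma, shape 4 (moderate skew) | 12.5% | 5.4% |
| Exponential | 5.6% | 1.8% |
| t(3) | 3.8% | 0.9% |
| Normal, for reference only | 17.9% | 8.9% |

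Repeat runs differed by up to 0.4 percentage points. The benchmark is 2.5% if the 95% CI is two-sided, or 5% under the one-sided alpha of the sample-size section.

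**4. The mismatch also runs the other way.** At a true deficit of 1 unit (inside the margin), exponential data and 22 per arm, 16.7% of trials give a significant Mann-Whitney result although the t-based 95% CI lies wholly above -2.

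**5. Methods that do address the margin.** At a true deficit of 2:
- The Welch 95% CI gives false noninferiority in 2.1% to 2.7% of trials across normal, gamma, exponential and t(3) data.
- A Mann-Whitney test shifted by the margin gives 2.3% to 2.6% at one-sided .025, and 4.7% to 5.0% at one-sided .05, under normal, exponential and t(3) data.

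**6. How often the branch might be used.** The plan does not name the normality check. Assuming Shapiro-Wilk at .05 in each arm (6,000 simulated trials), the switch occurs in about 10% of trials with truly normal data, 43% (17 per arm) to 55% (22 per arm) with moderate skew, and over 93% with exponential data.

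**The case against.** The strongest reply is that the sentence setting the mean difference and its 95% CI against the margin carries no normality condition. On that view the rule always applies, and the article has merely left the interval for one branch to a fuller analysis plan. This stands only in part. The next paragraph ties the interval to normally distributed data and names a different procedure for the rest. The article therefore fixes a fallback that does not serve its own rule, which is more than an omitted detail.

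Other parts of the reply do stand, and they rule out stronger readings:

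- **That noninferiority could not be decided by any rank method.** A margin-shifted test or a Hodges-Lehmann CI would decide it. The gap belongs to the fallback as written.
- **That the plan treats non-significance as noninferiority.** The document never says so, and the error rates above are conditional on that reading.
- **That the inflation is 18% or 9%.** Those are the normal-data rates, and the branch is meant for data that are not normal. There the rate depends on shape. At 22 per arm it is below 2.5% for exponential and t(3) data.
- **That RCT2 has the same defect.** RCT2 tests a superiority main effect against no difference, which a rank-based test can address. Its 2-unit superiority margin appears only in the sample-size text, and the interaction is only explored.

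The article also reports that data analysis was completed in May 2025, so a change now is a departure to be disclosed and not a simple edit.

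**Conclusion.** The point holds for RCT1. When normality is not verified, the stated rule for the primary outcome cannot be applied, because the named test provides neither a mean difference nor an interval to set against -2.

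The certain consequence is a primary analysis with one branch that has no decision rule. Inflated error is conditional. It requires someone to read p>.05 as noninferior, and its size then runs from about 13%/5% (moderate skew) to 4%/1% (t(3)) at 17/22 per arm. These figures rest on SD 1.9, a pure location shift and equal spread in the two arms. The 2.5% benchmark assumes that the 95% CI is two-sided.

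For RCT2 there is only a minor reporting point: rank-transformed ANCOVA gives no effect in GMFM-66 units.

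**What to change.** **RCT1 primary outcome.** Replace the normality-triggered switch with one rule. Report the difference in mean GMFM-66 change (home minus on-site) with its 95% CI from the Welch method, or from a bootstrap of the same mean difference if the data are clearly non-normal. Conclude noninferiority only if the lower limit is above -2. The estimate and margin then stay the same whatever the normality check shows.

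A Hodges-Lehmann shift with its CI, or a Mann-Whitney test shifted by the margin, can be added as sensitivity. The text should say that the 2-unit margin is being applied to a shift, which equals the mean difference only under a location-shift model.

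**RCT2 (minor).** If rank-transformed ANCOVA is used, report alongside it the ANCOVA estimate in GMFM-66 units with a robust or bootstrap CI.

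**Cost.** A few sentences, a small re-analysis with standard methods, and a disclosed departure from the stated method. The Results section says analysis was completed in May 2025 and that submission is still to come, so the publication should state that the change was made after analysis and also show the result of the method first planned.

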#### RCT2: Low- to Moderate-Dosage Home Follow-Up Interventions (9-Weeks HABIT-ILE@home Follow-Up vs Nonspecific Home Follow-Up)

Changes within each group during follow-up (T2-T1) will be assessed using paired-sample *t* tests when data are normally distributed, or Wilcoxon signed-rank tests in the case of nonnormal distributions.

The superiority analysis will be based on between-group comparisons using an analysis of covariance (ANCOVA) model. For each outcome, the model will be specified as outcome at T2 ~ outcome at T1 + RCT1_group × RCT2_group. This model will include the baseline value at T1 as a covariate and will test the main effects of the initial intervention (HABIT-ILE@home vs on-site), the follow-up intervention (HABIT-ILE@home follow-up vs nonspecific home follow-up), and their interaction. This approach will allow the effect of the second randomization (RCT2) to be evaluated while accounting for the initial allocation in RCT1.

The inference for superiority will be based on the main effect of RCT2_group (HABIT-ILE@home follow-up vs nonspecific home follow-up), adjusted for T1 values and RCT1_group. The interaction term (RCT1_group × RCT2_group) will be examined to explore whether the effect of the follow-up intervention differs depending on the initial intervention.

For normally distributed outcomes, model assumptions will be checked and standard ANCOVA estimates will be used. If normality is not verified, a nonparametric alternative based on rank-transformed ANCOVA will be applied.

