### Aims and Hypotheses

Two randomized controlled trials (RCTs) are described in this protocol. The first RCT (RCT1) aims to evaluate whether a high-dosage HABIT-ILE telerehabilitation intervention (HABIT-ILE@home) can achieve improvements in motor and functional abilities, as well as in social participation and neuroplastic changes comparable to those obtained with a conventional high-dosage HABIT-ILE on-site camp in children with bilateral CP aged 5-18 years. Gross motor function, assessed using the Gross Motor Function Measure-66 (GMFM-66), will constitute the primary outcome measure. We hypothesize that significant improvements in gross motor function will be observed in both groups after the 2-week intervention and that improvements achieved following HABIT-ILE@home will be noninferior to those observed after the HABIT-ILE on-site camp.

The second RCT (RCT2) aims to determine whether a structured low- to moderate-dosage HABIT-ILE@home follow-up program provided over 9 weeks leads to greater retention and further improvement in motor and functional abilities as well as in social participation, compared to a nonspecific home follow-up intervention based on usual clinical practice following the intensive HABIT-ILE intervention. Gross motor function assessed using the GMFM-66 will constitute the primary outcome measure. We hypothesize that children receiving the specific HABIT-ILE@home follow-up intervention will demonstrate greater retention and additional improvements in gross motor function compared with children receiving the nonspecific home follow-up intervention.

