## Methods

### Study Design

For RCT1, 44 participants will be randomized to 1 of the 2 groups (“HABIT-ILE@home” or “HABIT-ILE on-site camp,” 65 h for 2 wk), 22 children per group (Figure 1). The HABIT-ILE on-site camp will take place in Belgium with the presence of interventionists and a supervision team, whereas the HABIT-ILE@home intervention will take place at the children’s home with the constant presence of a caregiver (eg, parents, relatives, or other close individuals) and intermittent remote supervision. After this high-dosage camp, each group will then be further randomized into 2 subgroups of 11 participants (RCT2). One subgroup will receive the specific HABIT-ILE@home follow-up (5h/wk, for 9 wk), while the other will receive a nonspecific home follow-up based on their usual therapist’s recommendations. Recommendations of practice schedule given to caregivers will be similar for both follow-up groups: 5 hours per week at home for 9 weeks. Participants will be assessed before (T0) and after (T1) the 2 weeks of HABIT-ILE high-dosage camp, as well as at the end of the 9-week follow-up (T2). This study protocol is reported in accordance with the SPIRIT (Standard Protocol Items: Recommendations for Interventional Trials) guidelines (Figure 2).

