### Randomization Process

At the end of the recruitment phase, children were paired by the investigators according to Manual Ability Classification System (MACS) level, Gross Motor Function Classification System (GMFCS) level, and age, in this order of priority. Within each pair, participants were randomly assigned a code number (1 or 2) using Research Randomizer. To ensure allocation concealment and limit selection bias, the correspondence between the code number and the intervention group was determined independently by a person from an affiliated laboratory who was not involved in recruitment, assessment, or intervention delivery. This person indicated whether code 1 corresponded to the control group or to the treatment group after the pairs and code numbers had been generated. For RCT2, participants within each group of RCT1 were randomized again according to the same procedure to either the HABIT-ILE@home follow-up or the nonspecific home follow-up group (Figure 1).

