#### Primary Outcomes

##### RCT1: High-Dosage Intervention (2-Week Home vs On-Site Camp)

The primary outcome measure for RCT1 will be the change in GMFM-66 observed after the 2 weeks of HABIT-ILE@home vs the HABIT-ILE on-site camp (T1-T0). The GMFM-66 evaluates children’s gross motor function skills through a large spectrum of tasks ranging from lying and rolling to walking, running, and jumping [26]. Linear measures (% of the full-range scale expressed in logits; from 0% to 100%) will be used to quantify clinical changes. Higher percentage values represent better gross motor function skills. The GMFM-66 item set version will be used as its responsiveness, reliability, and validity have been demonstrated in children with CP, including infants and toddlers [27,28]. The GMFM-66 assessments will be video-recorded and blindly assessed by trained examiners after study completion.

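### RCT2 is randomised within pairs on MACS, GMFCS and age, but its primary ANCOVA adjusts for none of them, so the CI may be wider than necessary

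*Protocol article*

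**What the plan says.** Under Randomization Process, "children were paired by the investigators according to Manual Ability Classification System (MACS) level, Gross Motor Function Classification System (GMFCS) level, and age", and for RCT2 "participants within each group of RCT1 were randomized again according to the same procedure". The second randomisation is therefore restricted on the same three factors, within each RCT1 arm.

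Under Statistical Analysis, RCT2, "the model will be specified as outcome at T2 ~ outcome at T1 + RCT1_group × RCT2_group". The text then explains: "This model will include the baseline value at T1 as a covariate and will test the main effects of the initial intervention", along with that of the follow-up and their interaction. The superiority inference is the RCT2_group main effect, "adjusted for T1 values and RCT1_group". The article thus fixes the covariate set and does not leave it open.

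The Statistical Analysis overview mentions the pairing variables only in connection with comparability of the groups at baseline.

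A further pre-randomisation value exists. Under Study Design, "Participants will be assessed before (T0) and after (T1) the 2 weeks of HABIT-ILE high-dosage camp", and T0 GMFM-66 is needed anyway because "The primary outcome measure for RCT1 will be the change in GMFM-66 observed after the 2 weeks" (Primary Outcomes, RCT1).

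**The concern.** Pairing makes the randomised groups alike on the pairing factors, so the true sampling variance of the group difference is smaller than under simple randomisation. A model that omits those factors does not see this. Whatever they explain beyond T1 stays in the residual, and the computed standard error is too large for the design. The trial has then paid for pairing without collecting the precision.

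What is at stake is precision in a small trial: 44 children randomised, and 32 if losses reach the level planned for. The sample-size section sets RCT2 against a 2-unit margin, where a modest change in CI width can matter. Bias and the type I error rate are not threatened.

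**Working it through.** **Inputs.** From Sample Size, RCT2: difference 3.75, margin 2, SD 1.9, two-sided α .05, 16 per group. From Study Design: 22 per group randomised. The article gives no correlation between T0, T1 and T2 and no prognostic strength for MACS, GMFCS or age given T1. Ranges are therefore shown, and 1.9 is taken as the residual SD of the planned model.

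**The plan's own figure.** With 3.75 − 2 = 1.75 and SD 1.9, 16 per group reproduces with a one-sided .05 t test (power 82%). Read literally, as two-sided .05 against the margin, the requirement is 20 per group and power at 16 is 71%. The comparisons below use the literal two-sided reading.

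**Planned model.** It has p = 5 parameters (intercept, T1, two group terms, interaction), with groups coded ±½ so that the RCT2_group term is the main effect. The 95% CI half-width is t(.975, N − p) × s × √(4/N).
- N = 32: 2.052 × 1.9 × 0.3536 = 1.38.
- N = 44: 2.023 × 1.9 × 0.3015 = 1.16.

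**Adding three pairing factors.** Now p = 8 and s = 1.9 × √(1 − R²), where R² is the share of residual variance they explain given T1 and the groups. Counting degrees of freedom only:

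| Partial R² | Half-width N = 32 | Half-width N = 44 | Power vs margin, 16 / 22 per arm |
|---|---|---|---|
| planned model | 1.38 | 1.16 | 71% / 85% |
| 0.10 | 1.32 | 1.10 | 75% / 88% |
| 0.15 | 1.28 | 1.07 | 77% / 90% |
| 0.25 | 1.20 | 1.01 | 82% / 93% |

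**Cost if they explain nothing.** Degrees of freedom alone understate this, because chance imbalance also inflates the variance. In simulations that pair children on the three factors within each RCT1 arm, the adjusted CI is about 3% wider at N = 44 and 5% wider at N = 32 when partial R² is 0. Break-even follows from 1 − 1/1.03² = 0.06 and 1 − 1/1.05² = 0.09, so roughly 0.05 to 0.10.

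**Is the unadjusted standard error too large?** In the same simulations, the planned model's nominal 95% CI covers about 96% to 97.5% of the time for partial R² from 0.10 to 0.25. The adjusted model stays near 95%. The planned interval is conservative in that range.

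**T0 as one further covariate.** Let each change have variance V = 3.61, of which a share m is measurement error, with true changes in the two periods independent and child level varying widely. The residual variance with T1 alone is V. With T0 added it is V(1 − m/2)(1 + m/2) = V(1 − m²/4), so the reduction is m²/4:
- m = 0.25: 1.6%
- m = 0.50: 6.25%
- m = 0.75: 14%
- m = 1: 25%

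Below about half, T0 adds little. At m = 0 it widens the CI by about 1.4% (N = 44) to 2% (N = 32).

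**All four together.** With imbalance allowed for, and taking four useless covariates, the width ratio is the ratio of t quantiles × √((N − 6)/(N − 10)).
- N = 44: 1.0037 × √(38/34) = 1.061, break-even 1 − 1/1.061² = 0.11.
- N = 32: 1.008 × √(26/22) = 1.096, break-even 0.17.

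Simulation gives +6.1% and +9.3%. Both slightly overstate the cost for factors balanced by pairing.

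**The case against.** The strongest reply is that nothing here is an error. ANCOVA on the value measured just before randomisation is standard, omission of pairing factors makes the analysis conservative, and sparing use of covariates is defensible with 32 to 44 children. GMFM-66 at T1 may already carry much of what GMFCS and MACS predict, in which case extra terms widen the interval. Power is also less tight than the figures at 16 per arm suggest: 22 per arm are randomised, the RCT2 analysis section names no margin, and against zero the assumed 3.75 units gives power above 99%. All of this stands, and it limits the point to efficiency.

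It does not remove the reason to analyse by the factors the trial randomises by. That choice follows from the design, and the worst-case cost for the three factors is small.

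A reader might infer two stronger things. One is that the interval is certainly wider than the data allow. The documents do not support this, because it turns on partial correlations they do not report. The other is that a question about retention cannot be answered without T0. That also fails: the RCT2 primary outcome is defined as the change from T1 to T2, and ANCOVA of T2 on T1 under randomisation estimates the matching contrast. Adding T0 would change precision, not the question.

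**Conclusion.** The point holds as one of efficiency and of consistency between design and analysis. The RCT2 model leaves out the factors used to restrict its own randomisation. Its effect estimate and test are valid, but its standard error is too large wherever those factors remain prognostic given T1. For partial R² of 0.10 to 0.25, the degrees-of-freedom calculation gives a half-width about 5% to 13% smaller (1.32 to 1.20 against 1.38 at N = 32) and 4 to 11 points more power against the 2-unit margin at 16 per arm. The net gain is somewhat smaller once chance imbalance is counted. Below a partial R² of roughly 0.05 to 0.10 there is no gain and a small loss. T0 is a weaker case: it helps materially only if measurement error makes up a large share of the change variance. These sizes assume a residual SD of 1.9 and prognostic strengths that the article does not state.

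**What to change.** Add MACS and GMFCS as linear scores and age as a continuous covariate to the RCT2 model, alongside T1 and the RCT1_group × RCT2_group terms. Keep the RCT2_group main effect and its CI as the inference, and include the same variables in the multiple-imputation model. T0 GMFM-66 may be added as one further covariate if measurement error is expected to dominate the change variance. All these variables precede the second randomisation, so they cannot bias the follow-up effect.

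No new data are needed. The cost is three degrees of freedom (four with T0) and, at worst, the widening shown above: about 3% to 5% for the pairing factors and up to about 6% to 9% for all four.

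Timing matters. The article reports that analysis was completed in May 2025. If the stated model has already been run, it should remain primary and the adjusted model be reported as a labelled sensitivity analysis. If an analysis plan fixed beforehand already names these covariates, the article should say so.

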##### RCT2: Low- to Moderate-Dosage Home Follow-Up Interventions (9-Week HABIT-ILE@home Follow-Up vs Nonspecific Follow-Up)

The primary outcome is the same but will correspond to the change in GMFM-66 observed over the 9-week home follow-up period (HABIT-ILE@home follow-up vs nonspecific follow-up), measured from the end of the 2-week intensive intervention to the end of follow-up (T2-T1).

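### The home-versus-camp term in the T2 model adjusts for T1, the initial intervention's own outcome, so it does not test the main effect of that intervention as stated

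*Protocol article*

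**What the plan says.** In the Protocol article's Statistical Analysis, the RCT2 subsection gives one model for each outcome: "outcome at T2 ~ outcome at T1 + RCT1_group × RCT2_group". It says the model will "include the baseline value at T1 as a covariate and will test the main effects of the initial intervention", and also those of the follow-up intervention and their interaction. Two further sentences bear on how the terms are meant to be used. The approach is said to allow "the effect of the second randomization (RCT2) to be evaluated while accounting for the initial allocation in RCT1", and "The inference for superiority will be based on the main effect of RCT2_group", adjusted for T1 and the first allocation. The interaction is to be explored. No separate interpretation is given for the RCT1 main effect.

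On timing, Study Design says "Participants will be assessed before (T0) and after (T1) the 2 weeks of HABIT-ILE high-dosage camp". Primary Outcomes defines the RCT1 outcome as the GMFM-66 change from T0 to T1, and the RCT2 outcome as the change from T1 to T2. The RCT1 analysis subsection compares the T0-to-T1 changes between home and camp, with a confidence interval set against the noninferiority margin.

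**The concern.** T1 is a proper baseline for the follow-up comparison, because it is measured before the second randomisation. For the home-versus-camp comparison it is a result of treatment. Conditioning on it subtracts whatever part of the home-versus-camp difference was already present at T1. The comparison that remains, between home and camp children with the same T1 score, is no longer protected by the first randomisation.

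The text nevertheless labels this term a test of the initial intervention's main effect, for every outcome. In the article it is the only stated test of initial delivery that uses T2 data. Reported under that label, it could show nothing when home children are still behind at T2. It could also appear to favour home delivery when they are behind or merely level.

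**Working it through.** **Inputs from the Protocol article.** Four cells of 11 children, N = 44 (Study Design). SD 1.9 GMFM units and a margin of 2 units (Sample Size, RCT1). Two-sided α = .05 is used for the model terms. The net RCT2 effect in the simulation is 3.75 − 2 = 1.75 units (Sample Size, RCT2).

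**Assumptions not in the article.** The SD of 1.9 is taken as the SD of change in each phase. Between-child SD is 4, 8 or 15. Measurement-error SD is 0 or 1, with the total SD of change held at 1.9. The plan gives no figure of its own for this test, so there is none to reproduce.

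**Step 1: what the coefficient estimates.** Let D1 and D2 be the home-minus-camp differences at T1 and T2, and b the slope of T2 on T1. In the planned model the RCT1 coefficient is

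D2 − b × D1.

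With b close to 1:
- D1 = −2, kept in full (D2 = −2): −2 − (−2) = 0
- D1 = −2, half kept (D2 = −1): −1 − (−2) = +1
- D1 = −2, faded completely (D2 = 0): 0 − (−2) = +2
- D1 = 0, difference arising only after T1 (D2 = −2): −2 − 0 = −2

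Only in the last case does the coefficient equal the true T2 difference.

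**Step 2: precision without measurement error.** With 22 children per RCT1 arm:
- T1-adjusted: SE = 1.9 × √(2/22) = 0.57. Coefficients of 1 and 2 are 1.75 and 3.49 SEs, giving rejection near 40% and 92%.
- T0-adjusted: the residual SD covers both phases, 1.9 × √2 = 2.69, so SE = 2.69 × √(2/22) = 0.81. A difference of 2 is 2.47 SEs, giving rejection near 67%.

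**Step 3: simulation.** 4,000 trials per setting, effect-coded factors, 39 residual degrees of freedom. Ranges run over the assumed SDs.

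| Home deficit of 2 at T1 | True T2 difference | T1-adjusted (planned) | Rejection | T0-adjusted | Rejection |
|---|---|---|---|---|---|
| Kept in full | −2 | +0.01 to −0.12 | about 5% | about −2.0 | 65% to 81% |
| Half kept | −1 | +0.9 to +1.0 | 33% to 41% | about −1.0 | 21% to 30% |
| Faded completely | 0 | +1.9 to +2.0 | 87% to 92% | about 0 | about 5% |

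A difference of −2 arising only after T1 is picked up by the planned model: coefficient about −2.0, rejection 91% to 93%.

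The small departures from 0, 1 and 2 come from measurement error pulling b below 1. At between-child SD 4 and error SD 1, b is about 0.947, and −2 + 0.947 × 2 = −0.11.

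**Step 4: the follow-up term.** In every setting the RCT2 coefficient averages about 1.75 under T1 adjustment. Rejection of zero effect is about 83% to 85%, against 54% to 70% under T0 adjustment. T1 is the right covariate for that term.

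**The case against.** The strongest reply is that nothing is decided on this term. The model belongs to the RCT2 superiority analysis, which rests on the RCT2 factor, and RCT1 group is there to account for the first allocation. For that purpose the model is valid and more powerful than a T0-adjusted one. The home-versus-camp question is answered separately from T0-to-T1 changes, where a 2-unit deficit at T1 would be seen directly. Neither the aims nor the expected findings state a home-versus-camp hypothesis at T2. All of this stands, and it limits the weight of the point. It does not rescue the sentence that says the main effect of the initial intervention will be tested.

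A reader might infer more than the document supports:
- *That the test always reads close to zero.* This holds only when the T1 difference is kept in full. With fading the sign reverses, and a difference that arises after T1 is detected.
- *That a null result will be taken as long-run equivalence of home and camp.* Nothing in the article says so, and its noninferiority reasoning uses a confidence interval against a margin.
- *That a home-versus-camp comparison at T2 is a required analysis left out of the plan.* It is not a stated objective, so leaving it out is no error.

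**Conclusion.** The point holds as a mislabelled secondary test. The model as specified cannot deliver a test of the initial intervention's main effect at T2, because its covariate is that intervention's own outcome. This follows from the definitions of T1 and of the model and needs no assumption.

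The bias equals the T1 slope times the T1 difference. For a home deficit of the full 2-unit margin that is about 2 units, enough to hide the deficit or reverse its sign. The rejection rates depend on reading the SD of 1.9 as the SD of change in each phase and on the assumed between-child and measurement-error SDs. The pattern is the same across the range examined. Neither trial's primary conclusion is affected.

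**What to change.** Keep the T1-adjusted model for the RCT2 group effect and the interaction. Delete the statement that it tests the main effect of the initial intervention, and describe RCT1 group there as an adjustment factor only.

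If a home-versus-camp effect at T2 is to be reported, take it from a separate model, T2 ~ T0 + RCT1_group × RCT2_group, and give the RCT1 difference with its confidence interval. Label it secondary. The Results section says data analysis was completed in May 2025, so it must also be labelled post hoc. Submission of results is expected only in Fall or Winter 2026, so the report can still carry the correction.

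The cost is a wording change and, if wanted, one exploratory model on data already collected. No visits or participants are added, and the RCT2 inference does not change.
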